**Appendix**

**Table S1: Coding of covariates and outcome variables**

| **Clinical characteristic** | **Method of ascertainment** | **Description** |
| --- | --- | --- |
| Preeclampsia | ICD O11.1-5, O11.9 | Pre-existing hypertension with preeclampsia |
|  | ICD O14.0-2, O14.9 | Preeclampsia including HELLP syndrome |
|  | ICD O15.0-2, O15.9 | Eclampsia |
| Hypertensive diseases of pregnancy | ICD O13.1-5, O13.9 | Gestational (pregnancy induced) hypertension without significant proteinuria |
|  | ICD O11.1-5, O11.9 | Pre-existing hypertension with preeclampsia |
|  | ICD O14.0-2, O14.9 | Preeclampsia including HELLP syndrome |
|  | ICD O15.0-2, O15.9 | Eclampsia |
| Chronic hypertension | O10.0-4, O10.9 | Pre-existing hypertension complication pregnancy and the puerperium |
|  | ICD O11.1-5, O11.9 | Pre-existing hypertension with preeclampsia |
|  | ICD I10 | Essential (primary) hypertension |
|  | Check-box coding in the Swedish Medical Birth Register | Coded during antenatal care in response to “Chronic hypertension”, coded: “Yes” |
| Systemic lupus erythematosus (SLE) | Check-box coding in the Swedish Medical Birth Register | Coded during antenatal care in response to “SLE”, coded: “Yes” |
| Kidney disease | Check-box coding in the Swedish Medical Birth Register | Coded during antenatal care in response to “Kidney disease”, coded: “Yes” |
| Polycystic ovarian syndrome | ICD E28.2 | Polycystic ovarian syndrome |
| Gestational diabetes | ICD O24.4 | Gestational diabetes |
|  | Check-box coding in the Scottish Morbidity Records | In response to “Mother’s status of diabetes”, coded: “Yes, Gestational diabetes (diagnosed during pregnancy)” |
| Type 2 diabetes | E24.1 | Pre-existing type 2 diabetes mellitus, in pregnancy, childbirth and the puerperium |
|  | E11.0-9 | Type 2 diabetes mellitus |
| Congenital anomaly (neonatal) | Coded in the Scottish Morbidity Record | In response to “Congenital anomaly”, coded: “Acute life-threatening” “Non-life threatening” or “Yes” |
| Neonatal intensive care unit admission | Coded in Scottish Morbidity Record | In response to “Neonatal indicator”, coded: “Admitted for up to 48 hours” or “Admitted for more than 48 hours” |
| Neonatal death | Coded in Scottish Morbidity Record | In response to “Outcome of pregnancy”, coded: “Livebirth dying within the first six days of life” or “Livebirth dying on or after the 7^th^ day but before the 28^th^ day” |
| Body mass index | Scottish Morbidity Record | Calculated from maternal height and weight (weight (kg) / height (m^2^)) |
|  | Swedish Medical Birth Register |  |
| Smoking status | Coded in Scottish Morbidity Record | In reponse to “Smoker during pregnancy”, coded: “Yes” |
|  | Swedish Medical Birth Register |  |
| Socioeconomic status | Scottish Index of Multiple Deprivation | Recorded in quintiles |
| Maternal country of birth | Sweden Statistics | Coded as “Nordic countries”, “Europe & North America”, “Asia”, “Other” |
| Conception with in-vitro fertilisation | Check-box coding in the Swedish Medical Birth Register | In response to “IVF pregnancy”, coded: “Yes” |
| Highest level of maternal education | Education Register, Sweden Statistics | Coded as “University”, “Secondary school”, “<12 years of school attendance” |

Abbreviations: ICD = International Classification of Diseases

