**Table S2: Covariate balance: Standardized differences**

|  | | **Scotland cohort** | | **Sweden cohort** | |
| --- | --- | --- | --- | --- | --- |
|  |  | **Raw** | **Weighted** | **Raw** | **Weighted** |
| **Maternal age >35 years** | | 0.16 | -0.09 | 0.07 | -0.11 |
| **Smoking during pregnancy** | | -0.01 | 0.17 | -0.05 | 0.06 |
| **Body mass index >30kg/m^2^** | | 0.21 | -0.14 | 0.48 | 0.03 |
| **Year of delivery** | | 0.84 | -0.02 | 0.78 | -0.07 |
| **Maternal education** | | N/A | | -0.11 | -0.04 |
| **IVF pregnancy** | | N/A | | 0.03 | -0.06 |
| **Country of birth** | | N/A | | 0.14 | 0.02 |
| **Pre-existing medical condition** (chronic hypertension, renal disease, systemic lupus erythematosus) | | N/A | | -0.01 | -0.01 |
| **Chronic hypertension** | | 0.03 | -0.05 | N/A | |
| **Polycystic ovary syndrome** | | 0.07 | -0.03 | N/A | |
| **Socioeconomic status (quintiles)** | **2** | 0.02 | 0.11 | N/A | |
|  | **3** | 0.05 | 0.01 |  |  |
|  | **4** | -0.10 | 0.04 |  |  |
|  | **5** | 0.00 | -0.03 |  |  |

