**Exposure**

Maternal metformin use during pregnancy will be identified through the Scottish National Prescribing Information System (PIS), which has been linked with the Scottish Morbidity Records. Metformin use will be further categorised as use ever, 0 – 12 weeks, 13 – 27 weeks, and 28 weeks onward. Metformin exposure will be assessed for timing, with only prescription prior to preeclampsia diagnosis included.

1. **Primary outcomes:**

Diagnosis of preeclampsia identified by codes O11, O14 and O15 according to the International Classification of Disease Tenth Revision.

Preeclampsia will be further classified by stratifying according to gestational age at birth; <37 weeks and <34 weeks.

Secondary outcomes:

- Gestational hypertension ICD-O13
- Neonatal birthweight: small for gestational age at birth or large for gestational age at birth (defined according to **1)** < or > 2 SD; adjusted for gestational age and offspring sex or **2)** birthweight centile calculated using GROW charts; <10^th^ percentile for SGA and >90^th^ percentile for LGA) (binary)
- Macrosomia; birthweight >4500g (binary)
- Neonatal intensive care unit admission (obtained via neonatal indicator variable)
- Major congenital abnormality (binary)
- Congenital renal anomaly (binary)
- Perinatal death (binary)
- Preterm birth

1. **Additional analyses:**

- Metformin exposure for any indication, compared to the total unexposed population (whether or not they were diagnosed with diabetes)
- It is anticipated that most women requiring metformin in pregnancy will have been prescribed this in the context of Gestational Diabetes or Type II diabetes. The main analysis has therefore been limited to diabetic women, to eliminate diabetes as a confounder
- By number of scripts filled for metformin (possibly reflects compliance)
- By dose, categorised as 1g and >1g

1. **Outline of statistical analysis**
   1. Descriptive analysis

Summary statistics of baseline characteristics of patients will be presented with mean (SD) used to describe normally distributed continuous variables, median (IQR) for skewed continuous variables, and n (%) for categorical variables. Univariate analyses will be performed for each of the variables of interest to be included in the model.

Population characteristics to be described for:

a) Overall cohort

b) Metformin exposed vs non-exposed cohort

| Characteristic | Descriptor | Total population | Metformin exposed | Metformin unexposed |

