| --- | --- | --- | --- | --- |
| **Age,** (years) | mean ±SD |  |  |  |
| **Age >35 years** | n (%) |  |  |  |
| **Body mass index** (kg/m^2^) | mean ± SD |  |  |  |
| **Body mass index >30mg/kg** | n (%) |  |  |  |
| **Ethnicity** | n (%) |  |  |  |
| **Smoking,** yes | n (%) |  |  |  |
| **Deprivation score**  1  2  3  4  5 | n (%) |  |  |  |
| **Pre-gestational disorders**  Hypertension  Cardiovascular disease  Autoimmune diseases  Diabetes  Type I  Type II  Renal disease | n (%) |  |  |  |
| **Year of birth**  2009  2010  2011  2012  2013  2014  2015  2016  2017  2018 | n (%) |  |  |  |
| **Gestational diabetes** | n (%) |  |  |  |

- 1. **Outcome analysis**

Potential estimators are (i) selection model, using inverse probability weighting (IPW); (ii) outcome model, using regression adjustment; (iii) doubly robust inverse probability weighted regression adjustment (IPWRA) models. Under correct specification, all the estimators should produce similar results. We will focus on IPWRA; selection model will be included in the IPW and outcome in regression (RA) model specification. We will combine both regression adjustment and augmented IPW in a doubly robust regression model. We will also perform RA, IPW and multivariate LR separately.

Model for exposure assignment using inverse probability weighted propensity scores derived from the logistic exposure model. Adequacy of balance achieved by PS weighting will be assessed using: (i) standardised mean difference for model covariates and variance estimates between exposure groups and (ii) propensity scores overlap. If unbalanced, we will explore measures such as: addition of interaction terms; different exposure models; use of alternate weighting structures (overlap or stabilized); and lastly propensity score-based trimming with the aim of achieving overlap if the propensity score distributions.

This will be performed for the overall cohort and then subgroup analyses will be performed.

The model will be created for each outcome with the final included covariates determined by the authorship team and informed by direct acyclic graphs (Fig S1, S2). Covariates to be considered:

1. Maternal age at delivery
2. Body mass index
3. Deprivation score
4. Ethnicity
5. Smoking status
6. Pre-existing maternal disease
7. Conception with assisted reproduction

All statistical analysis will be performed using StataSE version 17.0.

- 1. Handling of missing data

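### O11 is both a primary-outcome code and a route into the baseline covariate chronic hypertension, with no look-back rule; this can attenuate a real effect by an amount the document does not let a reader judge

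*SAP*

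**What the plan says.** The primary outcome (SAP, Primary outcomes) is "Diagnosis of preeclampsia identified by codes O11, O14 and O15 according to the International Classification of Disease Tenth Revision". Table S1 repeats O11 for preeclampsia and for hypertensive diseases of pregnancy, and lists the same line, "ICD O11.1-5, O11.9 | Pre-existing hypertension with preeclampsia", under chronic hypertension.

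The other routes into chronic hypertension in Table S1 are "O10.0-4, O10.9 | Pre-existing hypertension complication pregnancy and the puerperium", I10, and for Sweden only, "Check-box coding in the Swedish Medical Birth Register | Coded during antenatal care in response to “Chronic hypertension”, coded: “Yes". No Scottish check-box is listed, so in Scotland the covariate rests on O10, O11 and I10.

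The covariate list under Outcome analysis names only "Pre-existing maternal disease", with no codes and no dates. The weights come from this step: "Model for exposure assignment using inverse probability weighted propensity scores derived from the logistic exposure model". The main estimator also uses an outcome regression: "We will focus on IPWRA; selection model will be included in the IPW and outcome in regression (RA) model specification".

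Table S2 shows the covariate in the Scottish weighting ("Chronic hypertension | | 0.03 | -0.05", raw then weighted standardised difference). For Sweden it is part of a composite of pre-existing conditions (-0.01 raw and weighted). The only timing rule, under Exposure, applies to the metformin prescription and not to the hypertension code.

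**The concern.** A baseline covariate should not depend on the outcome. Every woman coded O11 is a case, and that code alone sets her covariate to 1. A chronically hypertensive woman in Scotland who does not develop preeclampsia enters only through O10 or I10. Capture of the covariate can therefore differ by outcome status. If metformin lowers superimposed preeclampsia, it also lowers the apparent frequency of the baseline condition in the exposed group, and weighting then corrects for part of the effect under study.

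The doubly robust estimator gives no protection as planned, because the same covariates may enter both the exposure model and the outcome regression. The research question asks whether metformin reduces preeclampsia, and attenuation would tend to hide such a reduction.

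**Working it through.** **The document's own figure.** Table S4 gives preeclampsia in 18/637 exposed and 77/2,672 unexposed women. RR = (18/637)/(77/2672) = 0.98. SE(log RR) = √(1/18 − 1/637 + 1/77 − 1/2672) = 0.258, so the 95% CI is 0.59-1.63, as printed. The weighted RR of 0.96 (0.47-1.95) cannot be reproduced without patient data.

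**Size of the possible bias.** The document gives neither the number of O11 cases nor the capture by O10/I10, so these are assumed:
- true chronic hypertension c = 3% or 6%, equal in both groups (no confounding; the crude RR equals the true RR);
- preeclampsia risk in the unexposed 20% with and 2.4% without chronic hypertension, so O11 makes up 20% (c = 3%) or 35% (c = 6%) of cases;
- every chronically hypertensive case is coded O11;
- a proportion s of chronically hypertensive non-cases is captured by O10/I10;
- exposed share 637/(637 + 2,672) = 0.193.

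Let X = 1 if the woman is coded O11, or is chronically hypertensive and captured. The weighted RR is Σₓ P(X=x)·P(case | exposed, x) ÷ Σₓ P(X=x)·P(case | unexposed, x).

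Worked case: true RR 0.70, c = 3%, s = 0.30.
- Exposed, X = 1: cases 0.03 × 0.20 × 0.70 = 0.0042; non-cases 0.03 × 0.86 × 0.30 = 0.00774; risk 0.0042/0.01194 = 0.352.
- Exposed, X = 0: cases 0.97 × 0.024 × 0.70 = 0.016296; risk 0.016296/0.98806 = 0.01649.
- Unexposed, X = 1: cases 0.0060; non-cases 0.03 × 0.80 × 0.30 = 0.0072; risk 0.0060/0.0132 = 0.455.
- Unexposed, X = 0: cases 0.02328; risk 0.02328/0.9868 = 0.02359.
- P(X=1) = 0.193 × 0.01194 + 0.807 × 0.0132 = 0.01296.
- Weighted risks: exposed 0.02084, unexposed 0.02918. RR = 0.714.

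True chronic hypertension is equal in the groups, yet X is 1.19% in the exposed and 1.32% in the unexposed. The effect itself makes that difference.

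| Capture s | True RR 0.70, c = 3% | True RR 0.70, c = 6% | True RR 0.50, c = 3% to 6% |
|---|---|---|---|
| 0 | 0.758 | 0.798 | 0.59-0.66 |
| 0.30 | 0.714 | 0.724 | 0.52-0.53 |
| 0.50 | 0.707 | 0.712 | 0.51 |
| 0.75 | 0.703 | 0.704 | 0.50-0.51 |
| 1 | 0.700 | 0.700 | 0.50 |

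With a true RR of 1.00 every entry is 1.000. A second grid held preeclampsia at 2.9% in the unexposed, with chronic hypertension 2-4% there, risk 10-30% among those women, and some imbalance between groups allowed. For a true 0.70 it gave 0.717-0.818 at s = 0 and 0.701-0.720 at s = 0.50. For a true 1.00 it gave 0.995-1.000.

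**What deleting O11 would do.** Now assume chronic hypertension is 1.3 times as common in exposed women, and 30% is captured by O10/I10 whatever the outcome. The range runs over c = 3% to 6% in the unexposed.

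| True RR | O11 kept | O11 deleted |
|---|---|---|
| 0.70 | 0.712-0.720 | 0.727-0.746 |
| 1.00 | 0.993-0.996 | 1.038-1.065 |

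At 10% capture and a true 0.70 the two are close (kept 0.730-0.750, deleted 0.734-0.758). With no capture, keeping O11 is worse (0.755-0.794 against 0.738-0.764).

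**The case against.** O11 by its own description denotes pre-existing hypertension, so it identifies a genuine confounder as well as an outcome. O10 and I10 are also listed, so zero capture is an extreme that assumes away two of the three ICD routes. At 50% capture or more the shift on a true 0.70 is about 0.01 (at most 0.02 on the wider grid), small against the Table S4 interval of 0.47-1.95. The 6% scenario implies 3.5% preeclampsia in the unexposed (0.06 × 0.20 + 0.94 × 0.024), above the 2.9% in Table S4. All of this stands and limits the size of the bias. It does not remove the outcome dependence.

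A reader might infer more than the document supports:
- *That the RR is necessarily pulled toward 1.* This needs both poor capture and a real effect, and neither is documented.
- *That weighting forces equal numbers of superimposed preeclampsia in the groups.* Weighting acts on the whole covariate (O10, I10 or O11). Even that was not equalised: the Scottish difference went from 0.03 to -0.05.
- *That Table S4 shows the effect.* Weighting moves preeclampsia from 0.98 to 0.96, slightly away from 1, and hypertensive disorders from 0.86 to 0.96. All covariates are weighted together, so neither shift can be attributed to O11.
- *That deleting O11 is the remedy.* The second table above shows that this can leave more bias than it removes.

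**Conclusion.** The defect stands as a flaw of definition: one code family serves as outcome and as baseline covariate, and nothing in the plan stops the outcome from setting the covariate. The consequence is conditional. A true RR of 0.70 would be estimated as 0.71-0.72 at 30% capture and as about 0.80 at most if non-cases were never coded, under the assumed 3-6% prevalence and 20% against 2.4% risks. The most extreme corner of the wider grid reaches 0.82. With good capture, or with a true RR of 1, the bias is negligible. Where this study lies in that range cannot be determined, because the number of women classed by O11 alone is not reported. The near-zero standardised differences do not suggest a large bias, but they were computed on the affected covariate and do not exclude one. The point merits a change because the change is cheap, not because a large error has been shown.

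**What to change.** In both the exposure and outcome models, define chronic hypertension from information dated before 20 weeks: O10 or I10 on earlier records, the antenatal check-box for Sweden, and early antihypertensive dispensing in the linked prescribing data for Scotland. Do not use a code that requires preeclampsia. Keep O11 in the outcome. Do not merely strike O11 from the same-delivery code list, since that leaves confounding without replacing the information.

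Report the number of women, by exposure group, whose covariate is set by O11 alone, and give the RR with and without O11 in the covariate.

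The cost is a dated code list, a dispensing extract and a re-run. Some untreated or late-recorded chronic hypertension will be missed. The cohort is nulliparous, so earlier obstetric records will be few and Scotland will lean mainly on dispensing. The raw difference of 0.03 was computed with O11 included, so it does not show that this loss is small; the with-and-without comparison is needed for that reason too.

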**Null hypothesis**

Taking metformin during pregnancy does not affect the likelihood of developing preeclampsia among women with diabetes.

1. **Background**

Metformin is an oral hypoglycaemic agent prescribed to women in pregnancy with pre-existing Type II diabetes and gestational diabetes. It has well-described benefits for mother and neonate when used in this context [22]. Beyond diabetes, metformin has been reported to reduce the likelihood of pregnancy complications among women with polycystic ovary syndrome [23, 24], and in women with previous unsuccessful attempts at in vitro fertilisation (IVF) [25].

Compared with insulin, two meta-analyses concluded that metformin administration is associated with lower rates of preeclampsia[22], and pregnancy-induced hypertension [8]. However, in women with diabetes, studies in this area have been small. Population-based research with larger numbers could generate stronger evidence to better investigate this relationship.

The objective of this research is to determine the relationship between metformin and hypertensive disorders of pregnancy (preeclampsia, eclampsia, gestational hypertension) among women with diabetes, using a national population-based cohort from Scotland.

1. **Study population**

The population will include all nulliparous singleton pregnancies with a diagnosis of diabetes (gestational diabetes or Type II diabetes), recorded in the Scottish Morbidity Records between 2009 and 2018. The Scottish Morbidity Records hold data relating to pregnancy, delivery and perinatal outcomes for all women and infants discharged from maternity hospitals across Scotland.

Exclusion criteria:

a) Multifetal pregnancy

b) Parous women (to account for clustering)

c) Missing gestational age (which will be used to calculate gestational age at exposure)

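### Table S1 prints E24.1 for pre-existing Type 2 diabetes in pregnancy; the table's own logic points to O24.1, and this diagnosis is a route into the cohort

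*SAP*

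**What the plan says.** Additional File 1 of the SAP, under the study population heading, admits "all nulliparous singleton pregnancies with a diagnosis of diabetes (gestational diabetes or Type II diabetes". The overview of the main analysis repeats the same two diagnoses. Neither place gives a code.

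The codes are in Table S1 of the Appendix. Type 2 diabetes has two lines:

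- "E24.1 | Pre-existing type 2 diabetes mellitus, in pregnancy, childbirth and the puerperium"
- "E11.0-9 | Type 2 diabetes mellitus"

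Gestational diabetes also has two routes. One is a code, "ICD O24.4 | Gestational diabetes". The other is a Scottish Morbidity Records check-box: "In response to “Mother’s status of diabetes”, coded: “Yes, Gestational diabetes (diagnosed during pregnancy". No check-box answer is listed for Type 2 diabetes.

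**The concern.** The first Type 2 line pairs a pregnancy-specific label with a code from outside the block that the table uses for diabetes in pregnancy. This is more than a detail of a covariate list, because the diagnosis decides who enters the main analysis. If the printed code was the one searched for, the pregnancy route to Type 2 diabetes was closed and only E11.0-9 remained. Eligible women would then be absent from the cohort. Others, who also carry a gestational diabetes code or check-box, would enter but would not be recognised as having Type II diabetes in the planned baseline table. Whichever code was run, a reader who tries to rebuild the cohort from Table S1 would be using a wrong definition.

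**Working it through.** No formula in the plan bears on this point. The check sets the entries of Table S1 side by side and then follows a record through them.

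**1. Pregnancy-specific ICD entries in Table S1**

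- Chronic hypertension: "O10.0-4, O10.9 | Pre-existing hypertension complication pregnancy and the puerperium"
- Pre-existing hypertension with preeclampsia: O11
- Gestational hypertension: O13
- Preeclampsia: O14
- Eclampsia: O15
- Gestational diabetes: O24.4
- Pre-existing Type 2 diabetes in pregnancy: E24.1

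All but the last are in chapter O.

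**2. ICD entries for conditions not specific to pregnancy**

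- Essential hypertension: I10
- Polycystic ovarian syndrome: "ICD E28.2 | Polycystic ovarian syndrome"
- Type 2 diabetes, general: E11.0-9

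None of these has a pregnancy label. E24.1 is therefore the only entry in the table whose chapter and description disagree.

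**3. Closest parallel.** Chronic hypertension is also a pre-existing disease, and it too has both a pregnancy entry (O10) and a general entry (I10). Type 2 diabetes has the same structure, a pregnancy line followed by a general line (E11.0-9). The pregnancy line is the one with the unexpected letter. Changing E to O gives O24.1, in the block already used for gestational diabetes.

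**4. Following a record through the table as printed.** A woman enters the main cohort if she has at least one of E24.1, E11.0-9, O24.4 or the gestational diabetes check-box. Take a woman whose record has O24.1:

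- with an E11 code as well: she enters, identified as Type 2;
- without E11 but with O24.4 or the check-box: she enters, identified as gestational diabetes only;
- with none of the other three: she is not found.

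Only the third group is lost from the cohort.

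**5. Size.** Let N be the number of otherwise eligible women with Type 2 diabetes and p the share of them in the third group. If E24.1 was run, the loss is p × N. If O24.1 was run, it is 0. The document gives neither p nor N, so the loss can only be placed between 0 (p = 0) and N (p = 1). Table S4 covers 637 + 2,672 = 3,309 women with multiple metformin scripts or none, but does not split them by diabetes type or by code.

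**The case against.** The strongest reply is that this is a typing slip. The description makes the intention plain, one letter is wrong, and the document has similar slips elsewhere, such as a body mass index threshold in mg/kg in the baseline table. Table S1 is a printed table, not extraction code, and nothing shows that E24.1 was ever searched for. Its title refers to covariates and outcomes, and Additional File 1 defines the population in words without citing it.

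Much of this stands. The error may be in print only, and its effect on the data is unknown. What does not stand is that the table is mere background. It is the only place that gives codes for the diagnosis required for entry, so in practice it is the definition that a reader or programmer would use, and no other section corrects it.

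A reader might also infer more than the document supports:

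- **That women were in fact lost.** This depends on which code was run, which is not shown.
- **That the pregnancy code is the one mostly used in maternity records, or that unrelated E24 diagnoses were admitted.** The document says nothing about coding practice or about what E24.1 denotes.
- **That the loss falls on early metformin users or on higher-risk women.** Type 2 diabetes precedes pregnancy, so the thought is natural. But the exposure windows come from the prescribing data, not from ICD codes, and could be affected only through who enters the cohort. No count by diabetes type and exposure window is given.

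**Conclusion.** The printed code is wrong on the table's own evidence, and nothing elsewhere in the SAP corrects it. Used as printed, Table S1 would miss women identified only by the O24 code for pre-existing Type 2 diabetes. That is a defect in the operational definition of the cohort, but its consequence is conditional. It requires that the extraction used E24.1 and that some women had no other qualifying entry. Neither the number affected nor the direction of any change in the risk ratios can be derived from the document. The additional analysis of metformin for any indication against the total unexposed population does not require a diabetes diagnosis for entry, so its membership does not depend on this code.

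The conclusion assumes that Table S1 is the operational source for the diabetes diagnosis. That is reasonable, since no other diabetes codes are given, but the document does not say so.

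**What to change.** 1. Correct E24.1 to O24.1 in Table S1, after checking the code against the edition of the classification in use.
2. Confirm from the extraction code which of the two was searched for, and state this with the table.
3. Refer to Table S1 from the study population section of Additional File 1, so that the codes defining entry are explicit.
4. Only if E24.1 was run: re-extract the cohort, rerun the analyses that depend on it, and report how many women enter and how many change diabetes type.

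Steps 1 to 3 cost one character, one check and one sentence. Step 4 costs a re-extraction and a rerun, and arises only if the check shows that the error reached the data.
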